**Sample Size**

It is estimated that the substitution of atazanavir and increase in bilirubin will increase endothelium-dependent, flow-mediated vasodilation FMD by 3-4%. With an estimated standard deviation of the measurement of 4% and a 1:1 randomization scheme, this yields a power of 81-96% with a sample size of 60 subjects in a parallel design trial.

For aim 2, we expect a similar difference in FMD to be noted between the 30 subjects on atazanavir and the 60 subjects at study entry for the primary aim, thus making the comparison 1:2, yielding a power range of 87-99% to detect a difference in flow-mediated vasodilation.

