**Data and Statistical Plan**

[figure not shown]
The primary endpoint of this study will be endothelium-dependent, flow-mediated vasodilation of the brachial conduit artery in subjects randomized to atazanavir compared with subjects continuing their current therapy. Nitroglycerin-mediated, endothelium independent vasodilation will be a secondary endpoint. The analysis begins with descriptive and graphical summaries of each outcome measure at pre-treatment, treatment at 7 days, and post treatment and difference from pre to post treatment. The assessment of the normality of each outcome will be performed by plotting the raw data and transformation will be applied if necessary. The primary analysis of between-subject effects will be assessed using student t tests. Sample size calculation: This protocol will be powered to detect a statistically significant difference in both resistance arteriole and conduit artery studies. We will enroll 60 subjects for the randomized portion of this protocol. Thirty subjects will receive atazanavir and 30 will continue to receive their baseline ART. Nitric oxide accounts for 50-60% of the increase in vasodilation to reactive hyperemia (31). It is anticipated that atazanavir will improve absolute endothelium-dependent vasodilation approximately 3% during flow mediated vasodilation. (Please see the table to see a range of power based on effect.)

Analysis of markers of bilirubin, oxidant stress, inflammation, and insulin sensitivity: As key secondary endpoints, the analysis begins with descriptive and graphical summaries of each outcome measure at pre treatment, post treatment and difference from pre to post treatment. The assessment of the normality of each outcome will be performed by plotting the raw data and transformation will be applied if necessary. The primary analysis of between-subject effect will be assessed using paired student t tests. A Bonferroni correction will be applied to account for multiple comparisons. The relationship between changes in secondary markers and changes in vascular function will be assessed using multivariate analysis of variance (MANOVA).

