For the second protocol, vascular function for the 30 subjects stable on atazanavir will be compared to the baseline vascular function of the 60 subjects enrolled for the randomized protocol. The analysis plan, including descriptive and graphical summaries, testing of normality with transformation as needed, and between subject t testing will be applied similarly as in randomized trial.

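### Aim 2 carries the Student t test into a non-randomised 30 versus 60 comparison, where unequal variances would no longer be harmless; naming Welch's test is a cheap safeguard

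*Protocol*

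**What the plan says.** The Data and Statistical Plan sets the test for the randomised comparison of 30 versus 30: "The primary analysis of between-subject effects will be assessed using student t tests". Its closing paragraph, on the second protocol, says that "vascular function for the 30 subjects stable on atazanavir will be compared to the baseline vascular function of the 60 subjects enrolled for the randomized" part, and that "between subject t testing will be applied similarly as in randomized trial". That paragraph also carries over the descriptive and graphical summaries, the normality check and transformation. It mentions neither a variance check nor an unequal-variance test.

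The Sample Size section describes aim 2 as unbalanced ("thus making the comparison 1:2"). It gives one SD: "With an estimated standard deviation of the measurement of 4% and a 1:1 randomization scheme". There is no separate SD for either aim 2 group.

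The two groups are selected differently:
- **Third agent.** The 30 are all on atazanavir with ritonavir. The 60 may be on any approved PI other than atazanavir, an NNRTI or raltegravir (Trial Population; Key Inclusion Criteria).
- **Time on regimen.** More than 6 months for the 30 (Secondary Objectives); 3 months or longer for the 60 (Key Inclusion Criteria).
- **Bilirubin.** The exclusion for Gilbert's Syndrome or bilirubin above 1.5 mg/dL is limited to the randomised trial (Key Exclusion Criteria).

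**The concern.** The pooled test estimates one common variance, weighted towards the larger group. When the groups are equal in size, an error in the equal-variance assumption largely cancels out of the standard error. At 1:2 it does not. If the smaller group is the more variable, the pooled standard error is too small and there are too many false positives. If the larger group is the more variable, the standard error is too large, the test is conservative and power is lost.

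Randomisation gives equal variances under the null hypothesis of no treatment effect. Aim 2 has no randomisation, and its groups differ in ways that could affect spread. At stake are the error rate of the aim 2 test, the width of any interval built on the same standard error, and some power.

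**Working it through.** **Inputs.** Group sizes 30 and 60, a difference of 3 to 4 percentage points of flow-mediated vasodilation (FMD) and an SD of 4 come from the protocol. Two-sided alpha of 0.05 is an assumption. All unequal SD pairs are assumptions, shown in both directions.

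**The plan's own figures.** Noncentrality = difference / (SD × √(1/n₁ + 1/n₂)), pooled t test.
- Aim 1, 30 versus 30: 3 / (4 × √(1/30 + 1/30)) = 2.90, power 81.5%; for 4 points, 3.87, power 96.8%. Stated: 81-96%. This reproduces and supports the assumed alpha.
- Aim 2, 30 versus 60: 3 / (4 × √(1/30 + 1/60)) = 3.35, power 91.3%; for 4 points, 4.47, power 99.3%. Stated: 87-99%. The upper end reproduces. The lower end does not, but that is a separate matter and nothing below depends on it.

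**Bias of the pooled standard error.** Write s₁ for the SD of the 30 and s₂ for the SD of the 60.
- True variance of the difference: s₁²/30 + s₂²/60.
- Variance the pooled test aims at: [(29s₁² + 59s₂²)/88] × (1/30 + 1/60).

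For SDs 4 and 5: true 16/30 + 25/60 = 0.950, SE 0.975. Pooled (464 + 1475)/88 × 0.05 = 1.102, SE 1.050. The pooled SE is 8% too large.

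For SDs 5 and 4: true 25/30 + 16/60 = 1.100, SE 1.049. Pooled (725 + 944)/88 × 0.05 = 0.948, SE 0.974. The pooled SE is 7% too small.

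**Simulation.** Normal data, 30 versus 60, two-sided 5%, separate runs of 200,000 to 1,000,000 replicates per setting. Ranges show the spread across runs.

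| SD of 30 | SD of 60 | Pooled type I error | Welch type I error | Pooled power, 3 points | Welch power, 3 points |
|---|---|---|---|---|---|
| 4 | 4 | 5.0% | 5.0% | 91.2-91.3% | 90.9-91.0% |
| 4 | 5 | 3.5% | 5.0% | 82% | 86% |
| 3.5 | 5 | 2.8-2.9% | 5.0-5.1% | 86% | 90% |
| 5 | 4 | 6.8-6.9% | 4.9-5.0% | 84% | 80% |
| 5 | 3.5 | 8.1% | 5.0% | 88% | 82% |

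In the last two rows the higher pooled power comes from its inflated type I error, so it is not a real advantage.

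**Check that the 1:2 ratio is the cause.** With 30 versus 30 and SD ratios from 1 to 2, the pooled test stays at 5.0-5.2%. The same test is therefore adequate in the randomised part.

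**The case against.** The strongest objection is that the protocol does not clearly fix the pooled test. The second-protocol paragraph says only t testing, and Welch's test is a t test between groups. The plan also uses the Student label for paired tests, where no two-group variance is pooled, so the label may be generic. The variance form could be left to the SAP. This stands in part: the pooled form is a reading. But Student's t test ordinarily means the pooled version, and the plan expressly carries the randomised trial's testing over to aim 2. One sentence would settle it.

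A reader might infer that aim 2 has an inflated false-positive rate, or that a 5% level stated in the protocol is wrong. The documents support neither. No alpha appears in the readable text. Only one SD is given, and at equal SDs the pooled test holds 5%. A larger group on mixed regimens would, if anything, suggest more spread among the 60, which makes the pooled test conservative and costs power. The bilirubin exclusion, applied only to the randomised trial, could narrow the spread of the 60 instead. Neither effect is quantified, so the direction is open.

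It is also fair that the graphical summaries already planned would show a marked difference in spread. They do not say what test to use then, and choosing it after seeing the data is worse than naming it beforehand.

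Finally, aim 2 is a secondary, non-randomised comparison in which confounding is the larger threat. That stands, and it limits how much weight this point deserves.

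**Conclusion.** The point holds as a minor improvement. The Student t test, read as pooled, is robust to unequal variances in the 30 versus 30 comparison and loses that robustness at 30 versus 60, where group selection does not assure equal variances. For assumed SD ratios (30-group over 60-group) between 0.8 and 1.25, the type I error lies between about 3.5% and 6.9%. At 0.7 (3.5 versus 5) it is about 2.9%, and at 1.43 (5 versus 3.5) about 8.1%. Welch's test holds about 5% in all these cases.

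This rests on normal data, an assumed two-sided 5% level, assumed SDs, and the pooled reading of Student. If the SDs are equal, nothing is wrong with the test as named. The conclusion concerns aim 2 only.

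**What to change.** In the second-protocol paragraph of the Data and Statistical Plan, keep the existing sentence, because it also carries over the summaries, normality checks and transformation. Add after it: *For this comparison the between-subject t test will be Welch's unequal-variance t test.*

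The cost is one sentence. If the SDs are both 4, power at a 3-point difference falls by about 0.3 percentage points (91.3% to 91.0%), and at 4 points there is no visible loss. The sample size need not change. The added sentence does not make the two groups comparable; confounding needs separate treatment.
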